##### 12 weeks following treatment completion (sustained virological response or cure assessment):

The medical records of all participants confirmed through medical record review to have started DAA treatment will be reviewed to determine if they have had a sustained virological response (SVR) blood test anytime from 4 to 12 weeks following their treatment completion date.^33^ Reinfection will be differentiated from treatment failure due to relapse by assessing (1) genotype or subtype and (2) viral sequencing at a reference laboratory, whenever possible.Participants who have not had an SVR visit will be contacted by the study nurse approximately 12 weeks following the scheduled treatment completion date (determined by the date they received their script and duration of treatment) to request that they attend an SVR visit.

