##### 12 weeks following treatment completion (SVR)

SVR will be assessed as previously described for arm A.

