#### Control arm: SOC testing and treatment

All participants will be tested, treated and followed up according to the usual practice of the clinic for delivery of test results and ongoing HCV treatment. The participants’ medical record will be reviewed at the study close to assess testing and treatment uptake.

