### Study outcomes

The two primary outcomes of this trial include:

The proportion of participants commencing HCV treatment in each arm. Commencement of HCV treatment is defined as receipt of a script for treatment in arms A, B and control and as commencement of treatment with study drug in arm C. The proportion commencing treatment in each intervention arm will be compared with the control arm.The proportion of participants with HCV who start treatment achieving cure. Cure will be assessed by review of medical records for a clinic visit to assess SVR; if no visit has taken place, the study nurse will contact the participant to arrange one in all arms except the control.

Commencing treatment is an important and easily measurable outcome in clinical practice. The rationale for two primary outcomes is that arm C itself involves providing treatment to everyone found to have HCV as part of its intervention.

Secondary outcomes of this study include:

Time to treatment commencement is defined as number of days from first test to first dose of treatment.Case finding is defined as the proportion of people diagnosed with HCV among all those recruited.Cost-effectiveness is defined as the incremental cost to find and commence treatment among one person living with HCV from a health system perspective.

Participant acceptability is based on qualitative evaluation subject to further substudy design and ethical approval.

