### Statistical analysis

Results from the trial will be reported according to the CONSORT extension statement for cluster randomised trials,^38^ or a CONSORT extension statement for cluster randomised crossover trials if one is available prior to end of data collection. Clinic and patient demographics will be described by site and study period. Analyses will be conducted on an intention-to-treat basis, with patients analysed according to the randomised treatment of their cluster at the time of their inclusion in the study. All available binary outcomes will be analysed at the patient level using mixed-effects logistic regression models with random intercepts for clinic and clinic period and fixed effects for interventions.^39^ ORs and 95% CIs will be reported; in addition, we will calculate and report risk differences and 95% CIs.

There are three main comparisons proposed, namely, treatment uptake outcome in arm A versus control (comparison 1) and arm B versus control (comparison 2) and HCV cure in Arm C versus control (comparison 3). Incremental benefits of arm B to arm A, and arm C to arm B, and arm C to arm A on treatment uptake and HCV cure will be performed in subgroup analyses. Data from controls in each arm will be pooled and a single model fitted for each outcome.

Randomisation will occur in batches of six, performed by the coordinating centre and concealed from investigators and sites until after site governance approcal. Since randomisation is occurring within batches of six services, fixed effects for batch will be included in these models. The Kenward-Roger correction will be applied to adjust for the small number of clinics.^40^ Estimates of intracluster correlations (within-period and between-period) will be reported. Time-to-event outcomes such as time to complete diagnosis will be analysed using Cox proportional hazards models with shared-frailty terms for site and fixed terms for treatment group and randomisation batch. There may be imbalances between sites with respect to various clinic and patient-level characteristics, and secondary analyses will adjust for these.

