## Ethics and dissemination

### Ethical review

This study has been approved by the Alfred Ethics Committee (Number: HREC/64731/Alfred-2020-217547). Informed consent will be obtained from all participants prior to enrolment. Potential participants will be presented with detailed information about the study procedures, objectives, risks and benefits. Participants will be able to refuse or terminate participation at any time. Participants will be reimbursed US$40 at their baseline visit and US$80 for their SVR visit. Reimbursement will be by Coles/Myer voucher or by direct funds bank transfer (EFT/PayID).

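### Missing SVR tests are chased in arms A, B and C but not in control, so the primary cure comparison (arm C versus control) mixes cure with test attendance

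*Protocol article*

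**What the plan says.** All references are to the protocol article.

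- **Study outcomes** makes cure a primary outcome, assessed from a record of an SVR visit. Where there is none, "the study nurse will contact the participant to arrange one in all arms except the control".
- **Arm A, 12 weeks following treatment completion**, looks for an SVR test in the records "anytime from 4 to 12 weeks following their treatment completion date" and then adds the recall: "Participants who have not had an SVR visit will be contacted by the study nurse approximately 12 weeks following the scheduled treatment completion date".
- **Arms B and C** take this over by reference: "SVR will be assessed as previously described for arm A".
- **Control arm** follows usual clinic practice, and the participants' "medical record will be reviewed at the study close to assess testing and treatment uptake". No recall for SVR and no SVR window are given.
- **Ethical review** states without reference to arm: "Participants will be reimbursed US$40 at their baseline visit and US$80 for their SVR visit".
- **Statistical analysis** names cure in arm C versus control as comparison 3, one of three main comparisons, and analyses available binary outcomes. The passage that follows plans best-worst and worst-best scenarios for missing treatment-start data and similar ones for SVR.
- **The denominator for cure** differs between sections. The Abstract uses participants with HCV; Study outcomes uses those with HCV who start treatment.

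**The concern.** A cure can be recorded only if a test exists. The trial itself generates extra tests in arm C and none in control. Two participants who are equally cured and who both missed routine SVR testing can therefore be classified differently because of their arm alone.

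The recall is a measurement step, not part of the model of care under test. Arms A and B revert to usual clinic care after diagnosis and still receive it, and the Introduction defines the arm C model as point-of-care testing with same-day treatment. A difference in comparison 3 could therefore partly reflect how hard the trial looked for the outcome, and no later modelling of clinics or periods would separate the two.

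**Working it through.** **What the plan's own figures can and cannot show.** Sample size gives treatment start of 30%, 50%, 70% and 90% and cure of 10%, 30%, 50% and 70% in control, A, B and C. Cure divided by start is:

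- control 10/30 = 33%
- A 30/50 = 60%
- B 50/70 = 71%
- C 70/90 = 78%

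Planned cure is planned start minus 20 points in every arm. A, B and C share the same recall yet have different ratios, so the ratios do not measure ascertainment. The loss allowance (24/0.80 = 30 per site per period) is one figure for all arms and gives no testing rate by arm. The size of the bias therefore needs assumptions.

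**Assumed null scenario (no true difference).**

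- Start S = 0.30 in both arms (the planned control rate).
- True cure among starters q = 0.95 in both arms (the Introduction states above 90%).
- Share of starters tested in routine records s = 0.37, 0.50 or 0.70. The low value is the share that would produce the planned control rate at 90% efficacy: 0.10/(0.30 × 0.90) = 0.37.
- Share of untested starters successfully recalled in arm C f = 0.50; none in control.
- Tested share: control s; arm C s′ = s + (1 − s)f, that is 0.685, 0.75 and 0.85.

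**Formulas for the spurious difference, arm C minus control.**

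1. Starters, untested counted as not cured: q(s′ − s).
2. All with HCV, untested counted as not cured: S·q(s′ − s).
3. All with HCV, untested starters excluded: S·q·x/((1 − S) + S·x), evaluated at x = s′ minus x = s.
4. Starters, untested excluded: q − q = 0.

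For s = 0.37:

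- (1) 0.95 × 0.315 = 0.299
- (2) 0.30 × 0.299 = 0.090
- (3) 0.195/0.9055 − 0.105/0.811 = 0.216 − 0.130 = 0.086

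| Routine testing s | (1) | (2) | (3) | (4) |
|---|---|---|---|---|
| 37% | 29.9 | 9.0 | 8.6 | 0 |
| 50% | 23.8 | 7.1 | 6.3 | 0 |
| 70% | 14.3 | 4.3 | 3.4 | 0 |

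(points in favour of arm C)

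**When the direction changes.** Case (4) is zero only if recalled starters are cured as often as routinely tested ones. If recalled starters have 85% cure against 95%, arm C at s = 0.37 shows (0.37 × 0.95 + 0.315 × 0.85)/0.685 = 0.904, a difference of −4.6 points. Over s = 0.37 to 0.70 and recalled cure of 85% to 75%, the difference runs from −1.8 to −9.2 points.

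**What the planned sensitivity analyses would give.** Take s = 0.50 among starters, untested treated as missing, still with no true difference.

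- Best-worst: (0.75 × 0.95 + 0.25) − 0.50 × 0.95 = 0.9625 − 0.475 = +49 points.
- Worst-best: 0.7125 − (0.475 + 0.50) = −26 points.

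The scenarios bracket zero but are too wide to say how much of an observed difference is ascertainment.

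**The case against.** The strongest case against is about direction. Study outcomes sets starters as the denominator, the analysis uses available outcomes, and absent SVR is treated as missing data. On that reading untested starters drop out, and the spurious difference is zero or may run against arm C. This stands: a reader might infer that comparison 3 must be biased towards arm C, and the documents do not establish that. They do not settle on this reading either. The Abstract uses all participants with HCV, and planned cure of 10% versus 70% does not fit tested starters only, since efficacy above 90% would put every arm near 90%.

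Three further inferences are tempting and not supported.

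- **That the planned rates measure the bias.** Giving control arm C's ratio moves planned control cure from 10% to 0.30 × 0.778 = 23%, and 90% gives 27%, which suggests 13–17 of the planned 60 points. The 17 comes from raising control alone. With 90% in both arms the planned rates are 27% and 81%, a 54-point difference, so only 6 points change. Control start is also receipt of a script, so some control drop-off may be real non-initiation.
- **That a late test would be excluded in control.** The 4–12 week window is written for arm A and carried to B and C only. None is stated for control.
- **That control participants are not paid for an SVR visit.** The US$80 is not restricted by arm.

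The planned sensitivity analyses are a real mitigation, but they do not alter the primary estimate. If untested starters are scored as not cured, they are not missing and the scenarios do not reach them.

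**Conclusion.** The concern holds in this form: ascertainment of a primary outcome differs by arm, by explicit design, and comparison 3 therefore mixes cure with test attendance. The bias favours arm C in three of the four combinations of denominator and handling of untested starters. In the fourth (starters, untested excluded) it is zero or may reverse.

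Its size cannot be derived from the documents. Under the stated assumptions, counting untested starters as not cured gives about 4–9 points among all with HCV, or 14–30 points among starters. These figures rest on assumed routine-testing and recall rates and would shrink with higher routine testing or less successful recall.

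It does not follow that the planned effect is an artefact. Much of the planned 60-point difference reflects planned treatment start of 30% versus 90%: even if every planned control starter counted as cured, 70% versus 30% would leave 40 points among all with HCV. The asymmetry threatens the size of the cure effect and its interpretation, and should be corrected before cure is analysed.

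**What to change.** 1. **Equalise ascertainment.** Apply the same SVR recall procedure, timing and assessment window in control as in the other arms, with a window that admits recalled visits, and confirm that the SVR reimbursement applies there too. The cost is a protocol amendment and a modest number of nurse calls and vouchers for control starters, the smallest planned starter group (30%). Because the call comes about 12 weeks after scheduled treatment completion, it has little scope to alter standard care. There is a small chance of re-engaging control participants who were scripted but never started.
2. **Where control recall is no longer possible**, report cure from SVR tests found in routine records before any recall, with one window in all arms, as the like-for-like comparison beside the recall-based result. This needs analysis work only, provided that recalled tests can be identified in the data. Note its limit: routine testing may be lower where sites expect the study to recall participants, which would work against arm C.
3. **In either case**, fix one denominator for cure and one rule for starters without an SVR test, identical in all arms, and align the Abstract, Study outcomes and Statistical analysis with it. Report the share of starters with an SVR test by arm, split into routine and recalled. This costs wording and one table.

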### Sample size

Comparisons of primary interest are comparing outcome 1 (treatment commencement) in control and arm A; outcome 1 in control and arm B; and outcome 2 (HCV cure) in control and arm C. We consider sample size calculations with a minimum of 80% power and a significance level of 0.05/3=0.0167. Comparisons of control versus A are expected to result in the smallest required sample sizes so sample size calculations focus on this comparison. We use the Shiny CRT app^36^ for sample size calculations, assuming that the t- distribution is used instead of the normal approximation (accounting for small numbers of clusters).^37^

We suppose that five sites are assigned to each of the six treatment sequences. We found that with 24 participants recruited in each cluster in each period, power will be greater than 80% to detect a change in proportions of participants starting HCV treatment of 30%–50% where 10 clusters are allocated to arm A. Due to the greater portion of participants expected to start treatment in arm B (70%) and arm C (90%), power >80% is achieved with eight clusters assigned to the sequences that involve arms B or C (ie, with four clusters randomised to each of the arm B then control; control then arm B; Arm C then control; and control then arm C sequences). The proportion of participants expected to achieve cure in each arm are 10% among controls, 30% in arm A, 50% in arm B and 70% in arm C. Allowing for 20% loss to follow-up of sites and of participants, 30 participants per site per period would need to be recruited. Given these results, we will instruct sites to aim for 40 participants per site per period to counteract instances where some sites are unable to achieve 30 participants per site per period; some sites achieving 40 participants will balance sites which achieve <30. This would imply a maximum total of 2400 participants would need to be recruited.

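### The equal three-way alpha split gives up power on arm A, the weakest of the three main comparisons; Holm over the same three tests would recover it

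*Protocol article*

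**What the plan says.** The Sample size section of the protocol article sets "a minimum of 80% power and a significance level of 0.05/3=0.0167". It identifies the family: "Comparisons of primary interest are comparing outcome 1 (treatment commencement) in control and arm A; outcome 1 in control and arm B", and cure in arm C against control as the third. The Statistical analysis section numbers the same three as its main comparisons, and the hypotheses at the end of the Introduction match them.

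Sizing centres on arm A. With 24 participants per cluster-period and 10 clusters, "power will be greater than 80% to detect a change in proportions" from 30% to 50% starting treatment. Eight clusters are said to be enough for B and for C. Expected uptake is 70% in B and 90% in C; expected cure is 10% in control and 70% in C.

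For reporting, the Statistical analysis section says "ORs and 95% CIs will be reported; in addition, we will calculate and report risk differences and 95% CIs". It does not state the level at which the three comparisons will be judged. Under the primary outcomes, the Study outcomes section adds: "The proportion commencing treatment in each intervention arm will be compared with the control arm". That wording also takes in arm C on uptake, which is not among the three.

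**The concern.** An equal split suits comparisons of roughly equal strength. These are unequal by the plan's own figures: the expected differences are 20 points for A, 40 for B and 60 for C. Each is held to 0.0167 whatever the others show. If B and C are clearly positive and A has a p-value between 0.0167 and 0.05, A is declared negative, although a step-down procedure with the same family-wise error would accept it. What is at stake is a false-negative verdict on antibody testing alone, the simplest of the three models. The risk grows if sites are lost, and the plan itself allows for 20% site loss.

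A smaller point of wording goes with this. The Study outcomes section leaves open whether C versus control on uptake belongs to the confirmatory family, and any step-down procedure needs that family fixed first.

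**Working it through.** **Reproducing the plan's figures.** 0.05/3 = 0.0167. 24/0.8 = 30 per site per period. 30 sites × 2 periods × 40 = 2400. All three agree with the article.

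**Inputs from the article.** m = 24 per cluster-period; K = 10 clusters for A, or 8 after 20% site loss (10 × 0.8); uptake 30% control, 50% A, 70% B; cure 10% control, 70% C; t-based testing.

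**Assumptions, not in the article.** Two-sided tests; K − 2 degrees of freedom; ICC 0.01–0.20; CAC 0.5–0.8; all 24 participants count in the denominator; each arm is compared with control in its own clusters; the three statistics are independent.

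**Variance.** For a two-period cluster cross-over:

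Var = s² × [2(1 − ICC)/m + 2 × ICC × (1 − CAC)] / K, where s² is the mean of p(1 − p) over the two conditions.

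**Example, ICC 0.05, CAC 0.8, K = 10.** The bracket is 2 × 0.95/24 + 2 × 0.05 × 0.2 = 0.0792 + 0.0200 = 0.0992.
- A: s² = (0.21 + 0.25)/2 = 0.23; SE = √(0.23 × 0.0992/10) = 0.0478; 0.20/0.0478 = 4.19.
- B: s² = 0.21; SE = 0.0456; 0.40/0.0456 = 8.77.
- C, cure: s² = (0.09 + 0.21)/2 = 0.15; SE = 0.0386; 0.60/0.0386 = 15.6.

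With K = 8, A's ratio falls to 0.20/0.0534 = 3.75.

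**Power of B and C at 0.0167.** B ranges from 88% (K = 8, ICC 0.20, CAC 0.5) to over 99%. C on cure is above 99% throughout.

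**Holm.** Order the three p-values and compare them in turn with 0.0167, 0.025 and 0.05, stopping at the first failure. When B and C have the smaller p-values and both reject, A is tested at 0.05. Power of A from simulated noncentral-t statistics:

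| ICC | CAC | K = 10: Bonferroni → Holm | K = 8: Bonferroni → Holm |
|---|---|---|---|
| 0.01 | 0.5 | 87.1% → 96.5% (+9) | 70.6% → 89.5% (+19) |
| 0.01 | 0.8 | 89.4% → 97.4% (+8) | 73.7% → 91.4% (+18) |
| 0.05 | 0.5 | 72.6% → 89.3% (+17) | 54.4% → 78.0% (+24) |
| 0.05 | 0.8 | 84.5% → 95.4% (+11) | 67.3% → 87.4% (+20) |
| 0.10 | 0.5 | 57.6% → 78.7% (+21) | 41.0% → 65.3% (+24) |
| 0.10 | 0.8 | 78.2% → 92.5% (+14) | 60.0% → 82.4% (+22) |
| 0.20 | 0.5 | 38.7% → 60.9% (+22) | 26.5% → 47.3% (+21) |
| 0.20 | 0.8 | 66.5% → 85.4% (+19) | 48.5% → 72.8% (+24) |

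**Sensitivity.** At CAC above 0.8 A has more power to begin with and gains less: at ICC 0.20 and CAC 1.0 it goes from 95.9% to 99.3% (K = 10) and from 85.0% to 96.5% (K = 8). The degrees of freedom matter too. Under a normal approximation at ICC 0.05 and CAC 0.8, A has 96.4% at 0.0167 against 98.7% at 0.05 (K = 10), and 91.2% against 96.3% (K = 8).

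**Error rate.** With no effect in any arm, simulated family-wise error is 4.9% for both Bonferroni and Holm. Holm's bound of 5% does not need independence.

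**The case against.** Bonferroni at 0.0167 is correct arithmetic and valid error control, and the article claims more than 80% power for A with 10 clusters. That claim is attainable: at ICC 0.05 it needs a CAC of about 0.65 or more, at ICC 0.10 about 0.80. So the plan is not in error, and A is not shown to be underpowered. The analysis also pools controls across arms in a single model, which may give A more information and more degrees of freedom than assumed here; the gain would then be smaller. Both objections stand. They limit the size of the gain but not its direction, since Holm cannot reject fewer of the three than Bonferroni.

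Three stronger readings are tempting, and the article does not support them.

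- A reader might infer that the 95% intervals contradict the 0.0167 level and will inflate the error. Three independent tests read from 95% intervals would give 1 − 0.95³ = 14.3%. But the article says only that these intervals will be reported, not that claims rest on them. Unadjusted intervals beside an adjusted test are common, and the decision rule may sit in the statistical analysis plan, which is not shown.
- A reader might count four primary comparisons, with 1 − (1 − 0.0167)⁴ = 6.5% error if independent. The Introduction, Sample size and Statistical analysis sections all name the same three. The Study outcomes section also explains that cure is a second primary outcome because arm C supplies treatment as part of its intervention. What remains is one unlabelled sentence to reconcile.
- A reader might expect Holm alone to settle both matters at no cost. It does not. A 95% interval matches only Holm's last step, and the family must be fixed before Holm is applied.

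**Conclusion.** The point holds as an efficiency improvement with one reconciliation of wording, not as an error in the alpha calculation. Over the assumed range, replacing the equal split by Holm adds about 8–22 points to arm A's power with 10 clusters and about 18–24 points with eight, with family-wise error still at most 5%. These figures rest on ICC, CAC, sidedness and degrees of freedom that the article does not give, so they show what could be gained and are not the plan's own power. The gain also requires B and C to reject. If only one does, A is tested at 0.025; if neither does, A stays at 0.0167 when its p-value is the smallest, and little is gained.

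**What to change.** 1. In the statistical analysis plan, test the three named comparisons (A and B versus control on uptake, C versus control on cure) by Holm at a two-sided family-wise level of 0.05, and base claims on the Holm decisions.
2. Label the 95% intervals for these comparisons as unadjusted, or add 98.3% intervals (1 − 0.0167) beside them.
3. Reconcile the Study outcomes section with the Sample size and Statistical analysis sections by stating that C versus control on uptake is secondary and outside the three-test family.

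The cost is wording, with no change to recruitment or data collection. The Data monitoring section describes the statistical analysis plan as still under development, so the rule can be fixed before outcomes are compared by arm. The one real downside is that Holm decisions do not correspond to a single simple set of simultaneous intervals, so a Holm rejection can sit beside a 98.3% interval that includes the null. The plan should say that the test decision governs.

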**Methods and analysis:**

A cluster randomised cross-over trial will be conducted with three intervention arms and a control arm. Arm A will receive rapid hepatitis C virus (HCV) antibody testing; arm B will receive rapid HCV antibody and rapid RNA testing; arm C will receive rapid HCV antibody testing and same-day treatment initiation for HCV antibody-positive participants; the control arm will receive standard of care. The primary outcomes will be (a) the proportion of participants with HCV commencing treatment and (b) the proportion of participants with HCV achieving cure. Analyses will be conducted on an intention-to-treat basis with mixed-effects logistic regression models.

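### The arm A power figure pairs treatment-start rates that fit only people with HCV with a count of all recruits, so it holds only if an unstated share of recruits is HCV RNA-positive

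*Protocol article*

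**What the plan says.** The Sample size section asks for "sample size calculations with a minimum of 80% power" at "a significance level of 0.05/3=0.0167". Its main claim is that "with 24 participants recruited in each cluster in each period, power will be greater than 80" per cent to "detect a change in proportions of participants starting HCV treatment of 30%–50" per cent, "where 10 clusters are allocated to arm A". I read this as 30% under control and 50% in arm A.

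It then builds up recruitment: "Allowing for 20% loss to follow-up of sites and of participants, 30 participants per site per period would need to be recruited". Sites are told to aim for 40 so that strong recruiters offset weak ones, which gives a maximum of 2400 recruited.

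The abstract defines the first primary outcome as "the proportion of participants with HCV commencing treatment". The Study outcomes section omits the restriction to HCV for that outcome. It also lists a secondary outcome: "Case finding is defined as the proportion of people diagnosed with HCV among all those recruited". Under Participant eligibility, people qualify through any history of injecting; HCV infection is not required. In arms A and B, people whose confirmatory results are negative finish the study at weeks 0–2, and the week 12 review of prescriptions is headed as applying to RNA-positive participants.

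**The concern.** The rates and the count refer to different groups. Start rates of 30%, 50%, 70% and 90%, and a 70% cure rate in arm C, could not be rates among all recruits unless nearly all were infected. The article itself describes arm C as treating everyone found to have HCV. The 24 per cluster-period, however, is a number recruited before HCV status is known. If only a fraction f of recruits are RNA-positive, the control versus arm A comparison rests on about 24f people per cell.

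Arm A versus control is one of three primary comparisons and the one on which the calculation is built. If f is low, a null result for rapid antibody testing could be taken as absence of effect when the trial had limited ability to detect one. Sites that count consents would not see the problem developing.

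**Working it through.** **Inputs from the article (Sample size):** alpha 0.05/3 = 0.0167; 30% versus 50%; K = 10 arm A sites, each with one control period; 24 per cell; 20% loss; target 40; a t reference distribution.

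**Inputs assumed, because the article does not give them:** two-sided test; within-period ICC ρ = 0.05; cluster autocorrelation CAC = 0.8; degrees of freedom K − 2 = 8, with 2K − 3 = 17 as a variant; RNA-positive share f from 20% to 50%.

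**1. The recruitment chain reproduces.** 24/0.8 = 30, and 30 sites × 2 periods × 40 = 2400. Each step has a stated reason, and none is HCV positivity.

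**2. The power claim is attainable if all 24 count.** For m analysable people per cell:

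Var = s²[2ρ(1 − CAC) + 2(1 − ρ)/m]/K, with s² = 0.40 × 0.60 = 0.24.

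At m = 24: 0.24 × (0.0200 + 0.0792)/10 = 0.00238, so SE = 0.0488 and 0.20/SE = 4.10. The critical t on 8 df is 3.016, and the noncentral t gives 83% power (91% on 17 df). This agrees with the claim but does not reproduce it uniquely, since other ICC and CAC values also exceed 80%.

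**3. Restricting to RNA-positive people, pairwise.** With 30 recruited and 20% loss, m = 24f:

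| f | m | SE | Power, 8 df | Power, 17 df |
|---|---|---|---|---|
| 50% | 12 | 0.0654 | 55% | 66% |
| 40% | 9.6 | 0.0723 | 45% | 56% |
| 30% | 7.2 | 0.0825 | 35% | 43% |
| 20% | 4.8 | 0.0999 | 23% | 29% |

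At the 40 target less 20% loss, m = 32f, and the 8 df values are 67%, 58%, 45% and 31%.

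**4. The planned model.** The Statistical analysis section pools controls and fits one model per outcome. I approximated it by generalised least squares on cell means: 30 sites, five per sequence, a period effect and three intervention effects. Cell variance is s²[ρ + (1 − ρ)/m], covariance between a site's two periods is s²ρCAC, and df = 30 − 4 = 26 (critical t 2.559).

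| f | Power, 24 analysable recruits | Power, 32 analysable recruits (40 target) |
|---|---|---|
| 50% | 82% | 90% |
| 40% | 73% | 84% |
| 30% | 61% | 73% |
| 20% | 44% | 55% |

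Power reaches 80% at about 11.5 RNA-positive people per cell: f ≈ 48% of 24, or f ≈ 36% of 32. With ICC 0.01 the thresholds are about 41% and 31%; with ICC 0.10, about 57% and 43%.

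**5. If all recruits are the denominator instead.** The rates dilute to 0.3f versus 0.5f. At f = 50% this is 15% versus 25%: s² = 0.20 × 0.80 = 0.16, SE = √(0.16 × 0.0992/10) = 0.0398, 0.10/SE = 2.51, and pairwise power is about 37% on 8 df, against 55% in step 3. Averaging the arm-specific variances and using a shifted central t gives 32%.

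**6. The other primary comparisons.** With eight sites each, ICC 0.01–0.05 and CAC 0.8–0.9, the pairwise calculation (averaged arm-specific variances, shifted central t) keeps 80% power for arm B versus control (30% versus 70%) with about 4.2–5.9 RNA-positive people per cell, or f of 0.18–0.25 at 24 recruits. Arm C versus control on cure (10% versus 70%) needs f of only 0.06–0.08. The approximation is rough at such small cells, but the margin is wide.

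**The case against.** The strongest reply is that the pairwise figures describe an analysis the trial will not run. Pooling controls across 30 sites raises arm A power at 50% prevalence from 55% to 82%, and reaching 40 per period raises it to 90%. This stands, and the planned-model figures are the ones to judge by. Two limits remain: the Sample size section frames its claim on the ten arm A sites, and it justifies the 40 target by uneven recruitment, so sites that fall short use up that slack.

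The choice of 8 df is also on the pessimistic side. With 17 df the pairwise values rise by 6 to 11 percentage points, but at 50% prevalence they remain under 80%.

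A further reply is that a condensed article may use recruited loosely for participants with HCV, with the prevalence step set out in the full protocol. That cannot be excluded, but it fits poorly with a printed chain running from 24 to 30 to 40 to a maximum of 2400 recruited.

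Finally, the statement that only RNA-positive people can start treatment is not exact for arm C, where antibody-positive participants begin study drug before RNA confirmation. It is right for arm A versus control.

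**Conclusion.** The mismatch is established from the text: rates conditional on HCV are combined with a count of all recruits, with no factor for HCV positivity. The over-80% figure for arm A versus control therefore holds only if the unstated RNA-positive share is high enough. Under the planned pooled model, with ICC 0.05 and autocorrelation 0.8, that means roughly 48% at 24 analysable recruits or 36% at the 40 target. Taking the whole recruited sample as denominator makes power lower, so the looser outcome definition does not rescue the claim.

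A reader might infer that the trial fails to deliver its stated power, or that all three primary comparisons are underpowered. The documents support neither. Prevalence, ICC, autocorrelation and degrees of freedom are all unstated, at 40% prevalence and above the planned model exceeds 80% at the recruitment target, and the arm B and arm C comparisons tolerate much lower prevalence. The supportable conclusion is that arm A power is not shown, and is at risk if prevalence is low. It should be fixed.

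**What to change.** - Define the 24 per cluster-period as HCV RNA-positive participants, and use the same denominator for the first primary outcome in the abstract and in Study outcomes.
- State the assumed RNA prevalence among eligible attendees, the ICC, the cluster autocorrelation and the degrees of freedom.
- Restate arm A power and the detectable difference for the expected RNA-positive number per cell at 30 and 40 recruited, under the planned pooled-control model.
- Track recruitment by site-period in RNA-positive participants as well as consents.

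The cost is a change of wording, a re-run of the calculation, and an arm A power figure that is likely to look less favourable. No extra enrolment is required. Holding literally to 24 RNA-positive people after 20% loss would take 24/(0.5 × 0.8) = 60 recruits per site-period at 50% prevalence, or 60 × 60 site-periods = 3600 in all against the stated maximum of 2400. The fix does not ask for that; it asks that the power be stated for the numbers the trial expects to analyse.
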